## Abstract

**Background:**

Erythropoiesis and iron homeostasis are closely related; anemia due to lower-risk myelodysplastic syndromes (MDS) remains difficult to treat. In the last decade, we have been committed to improving the regulation of iron metabolism using traditional Chinese medicine (TCM). Previous studies have found that the TCM Yi Gong San (YGS) can reduce the expression of transferrin by inhibiting hepcidin overexpression caused by inflammation, promote the outward transfer of intracellular iron, and improve the symptoms of anemia. Here, our study aimed to compare the efficacy of a conventional drug with YGS with that of conventional medicine with placebo to provide a scientific basis for making clinical decisions.

**Methods:**

A prospective, multicenter, double-blinded, randomized controlled clinical trial will be conducted to evaluate the therapeutic efficacy of conventional medicine combined with YGS with that of conventional medicine alone in the treatment of MDS. A total of 60 patients would be enrolled in this study, with each treatment group (conventional medicine + YGS and conventional medicine + placebo) comprising 30 patients. Oral medication would be administered twice daily for 3 months. All patients would be followed up throughout the 3-month period. The primary outcome was measured by assessing blood hemoglobin level. The secondary outcome was measured by assessing TCM symptom score, iron metabolism, hepcidin levels, and inflammatory factors.

**Discussion:**

This trial would aim to demonstrate the effectiveness and feasibility of YGS in the treatment of lower-risk MDS anemia, as well as its impact on inflammatory factors and iron metabolism in patients with lower-risk MDS.

**Trial registration:**

Chinese Clinical Trials Registry (http://www.chictr.org.cn/) ChiCTR1900026774.  Registered on October 21, 2019.

## Background

Myelodysplastic syndromes (MDS) are a heterogeneous group of hematologic neoplasms characterized as a clonal disorder of the hematopoietic stem/progenitor cells leading to a host of hematological malignancies. MDS can be manifested as one or more morbid hematopoiesis of the bone marrow hematopoietic cells, ineffective hematopoiesis, and high-risk acute myeloid leukemia transformation [1]. Anemia is the most common clinical manifestation in patients with MDS. Approximately 60%–80% of patients have symptoms of anemia, and nearly 50% of MDS patients have severe anemia with an increased risk for heart and lung failure. Patients with International Prognostic Scoring System-Revised score of ≤3.5 has been categorized as lower-risk MDS subpopulation according to the 2012 International Working Group criteria. According to the European MDS statistics, lower-risk MDS accounts for approximately 70% of the entire MDS population, and most lower-risk MDS patients have symptomatic anemia; therefore, improving anemia and alleviating the symptoms of anemia are the main treatment goals for patients with lower-risk MDS [2].

The clinical treatment of lower-risk MDS anemia has always been a challenging task, despite the development of various treatment methods in Western medicine, including erythropoietin, immunosuppressants (cyclosporine A), immunomodulators (lenalidomide amine and thalidomide), and those undergoing clinical trials. A previous study reported that in patients with MDS anemia treated with the aforementioned drugs, 80–90% still require blood transfusion, and blood transfusion dependence (1 U red blood cell transfusion at least every 8 weeks within 4 months) is negatively related to patient survival [3].

Lower-risk MDS anemia, also known as ineffective hematopoiesis, is primarily caused by the excessive proliferation of red blood cell precursors, which fail to mature and impair the ability of red blood cells to carry oxygen in the blood. Additionally, erythropoiesis and iron homeostasis are closely related. Abnormal iron metabolism is an independent risk factor affecting the prognosis of patients with lower-risk MDS [2], and hepcidin plays a key role in iron homeostasis. MDS has a complex iron regulation mechanism: anemia, hypoxia, inflammation, and iron overload, which have opposite effects on hepcidin production. Compared with healthy individuals, patients with MDS deprived of blood transfusion have significantly increased serum ferritin (SF) and hepcidin levels, but have decreased hepcidin/SF ratio [4, 5]. In patients with lower-risk MDS undergoing blood transfusion, the hepcidin levels initially increase; however, as the amount of transfused blood increases, the hepcidin levels gradually decrease, eventually causing iron overload [6]. Iron overload would further aggravate the underlying hematopoiesis deficiency in those with MDS, making blood transfusion ineffective [2].

In the last decade, we have been committed to improving the mechanism of iron metabolism using traditional Chinese medicine (TCM). According to the TCM theory, spleen deficiency is an important triggering factor of MDS, and the approach called “tonifying the spleen” in TCM clinical practice is a crucial step of MDS treatment. The spleen is responsible for maintaining the normal distribution of iron in the body. The implementation of this function depends on the transportation of spleen *Qi*. Therefore, the deficiency of spleen *Qi* and the diminished function of spleen would cause an iron distribution disorder. Yi Gong San (YGS) is a representative TCM prescription for promoting the movement of spleen *Qi*. Previous studies have found that YGS used in TCM has no effect on iron metabolism in normal mice. However, it can reduce the expression of transferrin by inhibiting hepcidin overexpression caused by inflammation, promoting the outward transfer of intracellular iron and thus improving anemia [7–9]. Reports from many clinical trials have shown that YGS can improve inflammation-induced anemia (anemia due to chronic diseases) [10]. In fact, prior to blood transfusion, lower-risk MDS have the same pathological process of iron metabolism with anemia due to chronic diseases. However, it is not clear whether YGS is a suitable therapeutic candidate for anemia in patients with lower-risk MDS. Thus, this study aimed to compare the efficacy of conventional drug with YGS with that of conventional drug alone, as a basis for making clinical decisions.

## Methods

### Objective and design

This multicenter, pragmatic, randomized, and controlled trial is conducted to evaluate the effectiveness of integrating YGS into the conventional treatment for anemia in patients with lower-risk MDS. A total of 60 patients would be recruited and randomly assigned to one of the two treatment groups. During the treatment period, patients in both arms would be followed up for 3 months. The primary outcome (hemoglobin) and secondary outcome measures (TCM symptom score, iron metabolism, hepcidin levels, and inflammatory factors) would be assessed at different points within the trial period.

The study has been approved by the research ethics committee of the Shanghai Baoshan Hospital of Integrated Traditional Chinese and Western Medicine (#201809-01). This trial adhered to the Declaration of Helsinki and has been registered at the Chinese Clinical Trials Registry (ChiCTR1900026774) on October 21, 2019. The trial results would be reported according to the Standard Protocol Items: Recommendations for Interventional Trials statement and the latest version of the Consolidated Standards of Reporting Trials statement.

### Study setting and participants

All adult patients with lower-risk MDS admitted at the respiratory departments in three tertiary care hospitals would be screened and enrolled. Eligible patients would be asked to provide an informed written consent and would be centrally randomized to either the integrated YGS and conventional medicine group or the conventional medicine group. For both groups, all medications would be administered orally for 3 months (12 weeks). Patient recruitment has begun in March 2020 and should be completed in December 2021.

The inclusion criteria are as follows:
Patients aged > 18 years and olderPatients whose peripheral blood cell, bone marrow smear, gene, and chromosome profiles meet the criteria for lower-risk MDS according to the 2020 NCCN guidelines (V1)Patients with a hemoglobin level of < 110 g/LPatients whose symptoms meet the spleen *Qi* deficiency pattern of MDS according to the Standard Criteria for Syndrome Differentiation by TCM[11]

The exclusion criteria are as follows:
Patients who are blood transfusion dependentPregnant or lactating women, and women planning to become pregnant (must undergo urine pregnancy test, a standard test for women of childbearing age, before treatment)Patients with liver and kidney function insufficiency (whose blood aspartate aminotransferase, alanine aminotransferase, or creatinine concentrations exceed the normal value by more than 3 times the upper limit)Patients who recently participated in clinical trials of other drugs (within 2 weeks of TCM, within 7 half-lives of Western medicine)Patients with comorbidities that may cause anemia such as neoplastic diseasesPatients who are unwilling to cooperatePatients who cannot complete the specified observation items after being selected

### Randomization and double-blind approach

Participants who met the inclusion criteria and signed an informed consent form would be allocated to a group (Fig. 1). Based on a stratified block randomization design with a 1:1 ratio, two groups of patients would be assigned by the study center at the time of study. Allocation of patients is based on the random numbers (1 to 60) generated using an SPSS software version 25.0, and patient’s details are saved and kept in a sealed envelope by an independent clinical statistician based on the double-blind research method. In the study, the procedures of generating random numbers, evaluating the results of primary and secondary outcomes, and statistical analysis are independently performed by dedicated personnel who are blinded to outcome data. Upon completion of the study and data analysis, the efficacy and safety of YGS treatment shall be evaluated. During the clinical trial period, the treatment regimen of both study groups would be managed by their respective study center/hospital according to the approved treatment plan. If a patient develops a serious adverse reaction or life-threatening condition during the course of clinical trial, the clinician responsible for the patient must provide the best on-site medical care. Simultaneously, the clinician must immediately report the incidence to the inspector, upon which the letter containing patient’s treatment grouping information needs to be opened to break the blind, and the type of drug used is identified to ensure that the patient is provided with the appropriate emergency medical assistance. Once a blind is uncovered, the case would be regarded as a shedding case and would be excluded from the statistics, and any occurrence of adverse reactions would be recorded.

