### Data collection

Most patients in the outpatient clinic would be enrolled in the study. We would first obtain the patient’s informed consent. Then, we will collect the patient’s demographic data (sex, age, occupation, home address, diagnosis, and past history of illness) and help the patient fill out the TCM symptom scale to determine the type of symptom presented. A peripheral blood sample would be collected from each included patient prior to the initiation of treatment. The blood sample would be examined for various biochemical parameters such as liver and kidney function, iron metabolism-related indicators, hepcidin levels, and inflammatory factor-related markers. By randomly assigning them into either group, the patients would be administered with oral doses of conventional medicine with YGS or placebo for 3 months (12 weeks). At 1-, 2-, and 3-month intervals, the patients will be followed up in order to determine who among them would be suitable to fill up a new TCM symptom scale form to rate their symptoms, and a fresh peripheral blood samples would be collected (Table 2). Use case record form to collect patient clinical data and test data, and enter the information and data into electronic data capture.

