### Sample size considerations

Based on the sample size estimation formula (*n*1= *n*2 =2×[(μα+μβ)σ/δ]^2^+ μα^2^), the main research outcome indicator is the change in hemoglobin (Hb) levels, which will be used to estimate the sample size; compared with the baseline results, the Hb level of the experimental group (conventional medicine + YGS) increased to 20 g/L, while the Hb level of the control group (conventional medicine + placebo) increased to 14 g/L (standard deviation: 7 g/L, *n*1=group 1, *n*2= group 2, σ=14, δ=7, bilateral α=0.05, μα=1.96, unilateral β=0.2, μβ=0.84); therefore, each group should comprise 22 patients; considering a 30% loss due to follow-up, each group should comprise 30 patients. Therefore, we intend to recruit 60 patients from March 2020 to December 2021.

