### Statistical analyses

A descriptive statistical analysis of all the quantified variables in this study would be performed. The mean, median, and standard deviation will be calculated for quantitative variables, while the absolute and relative frequencies will be calculated for qualitative variables. The SPSS software (version 25.0; IBM Inc., USA) would be used for data processing and analysis. Statistical analysis would be based on the intention-to-treat and per-protocol population principles. The missing data can be processed using the last observation carried forward method. To compare the changes in TCM symptom scores and hematological data of patients before and after taking intervention treatment, multiple comparisons would be performed. A repeat measurement data analysis of variance will be initially conducted followed by a separate effect analysis, including comparisons between groups at each time point, using a multivariate logistic regression model to analyze the correlation between iron metabolism, hepcidin levels, and IL-6, TNF-α, IL-1 expression changes, and curative effect. Additionally, a subgroup analysis can be performed according to the R-IPI, and covariance analysis can be performed considering the factors such as age and sex. A two-sided *P* value of < 0.05 is considered significant.

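### Dropping every unblinded patient from the statistics contradicts the stated intention-to-treat analysis and can bias the haemoglobin comparison

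*Protocol article*

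**What the plan says.** Two sections of the protocol article bear on this.

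**Randomization and double-blind approach.** The trigger is "If a patient develops a serious adverse reaction or life-threatening condition during the course of clinical trial". The clinician reports the event, "upon which the letter containing patient’s treatment grouping information needs to be opened to break the blind". The consequence for the analysis follows: "Once a blind is uncovered, the case would be regarded as a shedding case and would be excluded from the statistics". The same sentence ends by adding that "any occurrence of adverse reactions would be recorded".

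**Statistical analyses.** "Statistical analysis would be based on the intention-to-treat and per-protocol population principles". For incomplete data, "The missing data can be processed using the last observation carried forward method". This section makes no exception for unblinded patients, and the randomisation section does not confine its exclusion to the per-protocol set.

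**The concern.** An intention-to-treat analysis keeps every randomised patient in the assigned arm. A patient who is out of the statistics is not in that analysis. Two analysts could follow this article faithfully and obtain different datasets: one deletes unblinded patients, the other keeps them.

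The deletion is also not neutral. It follows from a serious event after randomisation, and the event may depend on the treatment received. Patients with such events may plausibly have a poorer haemoglobin course. If the events are more frequent on YGS, the rule removes poor outcomes from the YGS arm and flatters it. If YGS prevents them, the rule flatters placebo instead. In either case the groups compared are no longer the groups randomised. With 30 patients per arm, a few deletions can move the primary comparison.

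**Working it through.** **1. The yardstick.** Sample size considerations gives mean haemoglobin increases of 20 and 14 g/L, a difference of 6 g/L, and an SD of 7 g/L in the text, with "bilateral α=0.05, μα=1.96, unilateral β=0.2, μβ=0.84". The usual two-mean formula gives

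n per arm = 2 × [(1.96 + 0.84) × 7 / 6]² = 21.34, rounded up to 22,

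which reproduces the stated 22. The planned difference is therefore taken as 6 g/L and the SD as 7 g/L. The same bracket also prints σ = 14 and δ = 7, which would give 63 per arm. That conflict is a separate matter, and the contradiction discussed here does not depend on it. After allowing for loss, the plan randomises 30 per arm.

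**2. The two rules side by side.**

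| Question | Randomization section | Statistical analyses section |
|---|---|---|
| Is an unblinded, randomised patient analysed for efficacy? | No | Yes, under intention to treat |
| Is the rule limited to one analysis set? | No limit stated | Two sets named, no exception stated |
| What happens to incomplete data? | Patient removed | Last value carried forward |

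No reading of the text as printed satisfies both columns.

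**3. Possible size of the shift.** The documents give no rate of serious events or unblinding, so the following inputs are assumptions:
- there is no true treatment effect, and the mean change is 14 g/L in both arms;
- k of the 30 YGS patients are unblinded and no placebo patients;
- the unblinded patients have no haemoglobin gain.

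The retained YGS mean is 14 × 30 / (30 − k), and the shift is that value minus 14.

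| k of 30 | Retained mean (g/L) | Shift (g/L) | Share of 6 g/L |
|---|---|---|---|
| 1 | 420/29 = 14.48 | 0.48 | 8% |
| 2 | 420/28 = 15.00 | 1.00 | 17% |
| 3 | 420/27 = 15.56 | 1.56 | 26% |
| 4 | 420/26 = 16.15 | 2.15 | 36% |

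More generally, if the unblinded patients lie g below their arm mean, the shift is k × g / (30 − k). With g = 7 it is 7/29 = 0.24 g/L (4%) for k = 1 and 21/27 = 0.78 g/L (13%) for k = 3. If both arms lose the same number of patients with the same deficit, both means rise equally and the difference is zero. If only placebo patients are lost, the shift has the same size and the opposite sign.

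**4. False-positive rate.** This used 20,000 simulated trials per setting, SD 7, a two-sided t-test at 0.05, and exclusions in the YGS arm only.

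| k | g (g/L) | Rejections with exclusion | Rejections with all kept |
|---|---|---|---|
| 1 | 7 | 5.4% | 5.1% |
| 1 | 14 | 5.8% | 4.2% |
| 2 | 14 | 8.2% | 3.6% |
| 3 | 7 | 6.9% | 4.2% |
| 3 | 14 | 13.1% | 3.0% |
| 5 | 14 | 30.5% | 2.1% |

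The last row is an extreme case. The right-hand column falls below 5% because the simulation fixes the number of low responders, which makes the t-test conservative.

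**The case against.** **The exclusion may be meant for the per-protocol set only.** That is a plausible intention, and a separate analysis plan may define the sets in detail. But the article states an explicit exclusion with no such limit, and any later plan would have to overrule one of the two sections. The contradiction stands.

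**The size is speculative.** This largely stands. The figures assume exclusions in one arm only, and the larger ones also assume that the excluded patients gained nothing. With one exclusion the false-positive rate hardly moves, and with balanced exclusions the shift disappears. The figures show what the rule permits, not what will happen.

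**The 30% allowance for loss covers it.** That allowance protects power. It does not protect against bias from selective removal.

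The documents do not support three stronger readings that a reader might infer:

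- *The intention-to-treat set consists only of patients who completed without complications.* The rule removes unblinded patients only. Carrying the last observation forward makes sense only if non-completers are kept, and the sample size plans for 30% loss.
- *Other wording removes randomised patients in the same way.* The criterion about not completing observation items stands in the list of exclusion criteria and reads as a loosely worded eligibility judgement. Nothing says that randomised patients are deleted under it. The Data collection wording, "determine who among them would be suitable to fill up a new TCM symptom scale form", concerns a secondary outcome. The same sentence provides for fresh blood samples, so haemoglobin is not tied to that judgement, and no analysis set is defined by it.
- *Safety information is lost and the benefit-risk statement is biased.* Adverse reactions in unblinded patients are recorded, and Adverse event reporting requires case report form entries and a serious adverse event form reported within 24 hours. The article does not say whether these events enter a safety analysis, so bias there is not shown.

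**Conclusion.** The exclusion rule is wrong as written. It conflicts with the article's own intention-to-treat principle, and it conditions the efficacy comparison on a post-randomisation event that treatment may affect. This conclusion rests on the text alone and needs no assumed rate.

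The size cannot be fixed from the documents. Under the stated one-arm, no-gain assumptions, the haemoglobin comparison shifts by about 0.5 to 2.2 g/L for one to four exclusions. If unblinding is rare, or balanced in number and outcome, the effect is negligible. The finding is confined to the unblinding rule and to efficacy.

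**What to change.** Replace the exclusion sentence with text to this effect: patients whose blind is broken remain in the intention-to-treat set and in the safety analysis; their haemoglobin data from the scheduled visits up to month 3 are collected where possible and analysed; unblinding is recorded as a deviation and may exclude a patient from the per-protocol set only. Refer to this rule under Statistical analyses so that the two sections agree.

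The cost is a few sentences in an amendment. The month 1, 2 and 3 visits are already scheduled, and the planned 30 per arm does not change. At 6 g/L and SD 7, power is 0.913 with 30 analysed per arm and 0.883 with 27 (normal approximation), so keeping these patients does not increase the required sample size. The Trial status section reports 19 patients recruited at submission, so the rule could be corrected before analysis. The procedure for emergency unblinding and the care of the patient are not affected.

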**Fig. 1 Fig1:**
[figure not shown]
Flow chart of the study design

### Intervention treatment

All patients would be treated with conventional medicine according to the MDS 2020 NCCN guidelines (V1) and TCM guidelines for the diagnosis and treatment of MDS (2019) [12]. For the conventional medicine and YGS treatment, patients would be given herbal interventions based on the spleen *Qi* deficiency pattern of MDS. YGS is an oral decoction containing five herbs: Ginseng Radix et Rhizoma (*Ren-Shen*), Glycyrrhizae Radix et Rhizoma (*Gan-Cao*), Citri Reticulatae Pericarpium (*Chen-Pi*), Atractylodis Macrocephalae Rhizoma (*Bai-Zhu*), and Poria Sclerotium (*Fu-Ling*). Granules containing these herbs are manufactured by Jiangyin Tianjiang Pharmaceutical Co., Ltd with strict compliance to Good Clinical Practice conditions in terms of the production process and packaging of mixed granules for TCM. Each YGS granule contains 20 g of each herbal raw material (Table 1).

**Table 1 Tab1:** Weight and composition of YGS and placebo granules

Chinese name (*pinyin*)	Latin name	Granule weight (g)	Herbal raw material weight (g)
Yi Gong San granules		**44.8**	
*Ren-Shen*	Ginseng Radix et Rhizoma	6.7	20
*Bai-Zhu*	Atractylodis Macrocephalae Rhizoma	14.7	20
*Fu-Ling*	Poria Sclerotium	6.7	20
*Chen-Pi*	Citri Reticulatae Pericarpium	8.2	20
*Gan-Cao*	Glycyrrhizae Radixet Rhizoma	8.5	20
Placebo granules		**44.8**	0

For the conventional medicine group, patients would be administered placebos containing maltodextrin, lactose, and food coloring, according to the modern pharmaceutical technology and placebo specification for granules. The placebos appear identical to YGS granules in terms of packaging, weight, odor, and color. In all patients, the medications would be administered twice daily, after breakfast and dinner, and up to 3 months (12 weeks).

